**Methods/design:**

HIPPO is a single-centre, double-blind randomized placebo-controlled study in patients with a radiologically confirmed diagnosis of gluteus medius or minimus tendinopathy with swelling within the tendon insertion with or without bursitis. We aim to randomise 102 patients with GTPS to either the PRP or placebo (normal saline injection) treatment arm. Participants will receive one ultrasound (US) guided PRP/placebo injection into the trochanteric bursa and surrounding gluteus medius/minimus tendons. The primary outcome measure is the International Hip Outcome Tool-12. Secondary outcome measures will include a visual analogue score for pain, the three-level version of the EuroQol five-dimensional questionnaire and the modified Harris Hip Score. Outcomes will be measured at baseline, 3, 6 and 12 months. Participants will have the option at 6 months to have a repeat blinded injection or cross over to PRP. Analyses of primary and secondary outcomes will be made according to the intention-to-treat principle. The trial reporting will comply with Consolidated Standards of Reporting Trials (CONSORT) guidelines.

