### Statistical analysis

#### Statistician report

The primary outcome of interest is the change from baseline to 12-month follow up in the iHOT-12, comparing the PRP and placebo group. The study will be run as a superiority trial. The cut-off for statistical significance is set at 5% and desired power at 90%, with two-tailed tests applied. Data on change from baseline are also assumed to be parametric and the *t* test will be applied to the data to assess statistical significance.

The minimally clinically important difference (MCID) for the iHOT-12 has been reported by Sansone et al. as 10 (from 100) and the standard deviation for the change in score from baseline as no greater than 21 [25]. Although, there are few previous data on which to base a sample size calculation, Monto et al. compared change from baseline to 12-month follow up in a group of 40 patient with hip bursitis, with steroids and PRP as the interventions being compared. In the PRP group Harris Hip scores increased from 51.7 to 87.4 whilst in the steroid group, scores increased from 50.5 to 58.8 at 12 months [22]. Since the Harris Hip score is also scored from 100, our sample size calculation is based on these figures. We conservatively assume that change in iHOT score from baseline in the placebo group will be no more than in the steroid group reported by Monto et al., and estimate a maximal change of 10. We also estimate that the change in the iHOT score from baseline in the PRP group will be no less than 27. Using these figures, a minimal sample size at follow up of 66 (33 in each group) will be required.

Pilot data obtained by our team suggest that the rate of refusal to participate should be no more than 25% and the dropout rate no more than 35% over 12 months. Refusal rates tend to be low in this patient group given the chronic nature of the condition and the fact that patients will only be approached once conservative management has failed. Thus, we will need to approach 135.4 (rounded up to 136) patients, and recruit 102 patients to achieve our target sample size.

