Data will be analysed using standard statistical software (e.g. SPSS and SAS). In the first instance, data will be analysed using simple descriptive statistics to compare the two groups in terms of demographics, clinical characteristics at baseline and outcomes. The primary outcome of interest will be the change from baseline to 12-month follow up in the iHOT-12, comparing the PRP and placebo group. The iHOT-12 data are expected to be parametric and so the unpaired *t* test will be used to compare the difference in change from baseline in the two groups. Since randomisation will not be stratified, we will also look to adjust for the possible confounding influence of differences in baseline characteristics (e.g. age, gender and body mass index (BMI)) using multivariable methods (e.g. linear regression). The significance level for all inferential tests will be set at 5%.

In secondary analysis, we will investigate changes in visual analogue pain score, EQ-5D 3 L and modified Harris Hip score in the two groups, as for the primary outcome. In sub-group analysis, we will investigate the data based on specific previous treatment, patients who required more than one treatment and patients with the highest levels of baseline pain.

The test group (PRP) alone: for all outcome measures the difference between the follow up scores with baseline will be assessed (e.g. baseline versus 3 months, baseline versus 12 months). The difference between one follow up period to the next will be examined (e.g. 3 months versus 6 months, 6 months versus 12 months). A significant difference will be set at a *p* value of less than 0.05.

The placebo group (normal saline) alone: data will be analysed as for the test group, as described.

Test versus placebo: for all outcome measures, the differential change at each follow up time point will be compared between the trial arms and the significance value calculated.

Statistical tests will be performed to ensure that gender, BMI and age differences are not significantly associated with a particular result. Care will be taken to minimise missing responses and to continue to follow up those who withdraw from treatment.

We will only be using the completed cases for final analyses; the remainder will be excluded.

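### The final analysis is limited to an undefined set of completed cases, against the stated intention-to-treat principle and with dropout of up to 35% allowed for

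*Protocol article*

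**What the plan says.** The Methods/design part of the abstract states: "Analyses of primary and secondary outcomes will be made according to the intention-to-treat principle".

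The Statistical analysis section defines the primary comparison: "The primary outcome of interest is the change from baseline to 12-month follow up in the iHOT-12, comparing the PRP and placebo group". The test is an unpaired t test. The section then ends with two consecutive statements that do not sit well together. The first is: "Care will be taken to minimise missing responses and to continue to follow up those who withdraw from treatment". The second is: "We will only be using the completed cases for final analyses; the remainder will be excluded".

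The same section sizes the trial for 33 per arm at 12 months and allows for "the dropout rate no more than 35% over 12 months", which gives 102 to be recruited. The Outcome measures section has iHOT-12 collected at baseline, 3, 6 and 12 months.

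**The concern.** The completed-cases sentence is a positive exclusion rule for the final analyses. It is not a detail left to a separate analysis plan. An analyst who follows it must drop randomised participants, and that conflicts with the abstract.

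The term itself is undefined, and two readings are open:

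- **A 12-month score is present.** Everyone lost before 12 months leaves the primary test, and their 3- and 6-month scores contribute nothing to it.
- **Treatment or all visits were completed.** The rule then also removes people who have a 12-month score. These could include the treatment withdrawers whom the plan undertakes to keep following.

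Loss related to response is plausible here. Participants have long-standing pain after failed conservative care. The Trial design section records the focus group's view that a further six months on placebo while in pain would be a significant burden. If that loss works differently in the two arms, the completer difference no longer estimates the effect in the randomised population, and the 5% error rate is not protected.

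**Working it through.** **1. The plan's own figures.** Inputs from the Statistician report: difference 27 − 10 = 17, SD of change 21, two-sided 5%, power 90%.

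- n per arm = 2 × (21 × (1.960 + 1.282) / 17)² = 32.07, so 33 per arm and 66 in total.
- Recruited: 66 / 0.65 = 101.5, so 102.
- Approached: 66 / (0.65 × 0.75) = 135.4, so 136.

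All agree with the article. The sample size is not at fault.

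**2. How many could be excluded.** At the stated ceiling, 102 × 0.35 = 35.7. About 36 would be left out and about 66 analysed.

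**3. When completers mislead.** In each arm let d be the share lost, and let g be the mean change of those lost minus the mean change of those who stay. The full-arm mean is the completer mean plus d × g. Therefore:

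bias of the completer difference (PRP − placebo) = d_placebo × g_placebo − d_PRP × g_PRP

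This is zero if d × g is equal in the two arms, whatever its size. Examples, with g assumed:

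| Loss PRP / placebo | g PRP / placebo | Bias (points) |
|---|---|---|
| 35% / 35% | −10 / −10 | 0 |
| 35% / 35% | 0 / −10 | −3.5 |
| 35% / 35% | −10 / 0 | +3.5 |
| 25% / 45% | −10 / −10 | −2.0 |
| 35% / 35% | −17 / 0 | +5.95 |

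**4. Effect on the error rate.** With 33 per arm, SE = 21 × √(2/33) = 5.17. With no true effect and a bias of 3.5, the bias is 3.5 / 5.17 = 0.68 SE. The two-sided rejection rate is then about 10%, nearly all of it in the direction of the bias. A bias of 2 gives about 7%, and 5.95 gives about 21%.

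**5. A concrete dropout pattern.** Assumed, not in the documents: 51 per arm, 35% lost in each arm, a correlation of 0.7 between 6- and 12-month change, SD 21 at both visits. One arm loses 55% of those below its 6-month mean and 15% of those above. The other arm loses at random.

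- Under normality, those above and below the 6-month mean differ from the arm's 12-month mean by ±0.7 × 21 × √(2/π) = ±11.73.
- Retention is 0.85 above and 0.45 below, so the completer mean in that arm moves up by 11.73 × (0.85 − 0.45) / (0.85 + 0.45) = 3.6 points.

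Simulated trials agree:

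| Arm with response-related loss | True effect | Result of completer t test |
|---|---|---|
| Placebo only | 17 | estimate 13.4, power about 73% (about 90% with random loss) |
| Placebo only | 0 | estimate about −3.6, about 11% rejections, of which 0.3 percentage points favour PRP |
| PRP only | 0 | estimate about +3.5, about 10% false claims for PRP |
| Both, same rule | 0 | estimate about 0, about 5% rejections |
| Both, same rule | 17 | estimate 16.3 (threshold common to both arms) to 17.0 (each arm's own mean) |

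Milder loss in the placebo arm only (45% / 25%) gives −1.8 with no true effect. Stronger loss (65% / 5%) gives about −5.4.

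**6. What the earlier scores recover.** In these scenarios loss depends only on the 6-month score, and everyone is assumed to have one. Using that score therefore removes the bias by construction (17.0 and 0.0). In a variant where placebo loss depends on the 12-month outcome itself, the completer bias with no true effect is about −5.1. Using the 6-month scores reduces it only to about −2.7.

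**The case against.** The strongest reply is that blinding makes the asymmetric scenarios unlikely. Blood is drawn from everyone, the centrifuge wait is simulated, and a drape and screen hide the injection. With no true effect and working blinding, the same loss rule should act in both arms, and the completer t test is then essentially unbiased. This stands, and it is why the shift of about 3.5 points is an unfavourable case and not a forecast. It does not rescue the rule, because equal loss mechanisms cannot be assumed in advance and the article describes no sensitivity analysis for missing data.

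One can also say that intention to treat only means analysing people in the arm to which they were allocated. But the rule removes people after randomisation, and the undefined term could reach people who have a 12-month score.

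Some stronger readings are tempting but not supported:

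- **That the plan expects 36 losses.** The 35% is given as a ceiling.
- **That any bias would be uncheckable.** The 3- and 6-month scores allow those lost to be compared with completers by arm, as far as they reached those visits.
- **That every early score is necessarily discarded.** The plan also compares arms at each follow-up, and that could be done visit by visit.
- **That an inflated error rate means false claims for PRP.** If the placebo arm is the one affected, nearly all the extra rejections favour placebo and the trial loses power. Only the mirror case produces false PRP claims.

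**Conclusion.** The abstract and the Statistical analysis section contradict each other, and the rule as written governs the primary result. Up to about 36 of 102 randomised participants could be excluded. The inflation from 66 to 102 keeps power near 90% if loss is unrelated to response, but it gives no protection against bias.

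The size of any bias is unknown. Under the assumptions in steps 3 and 5 it runs from zero, when loss and its relation to response are the same in both arms, to about 2 to 6 points in either direction when they differ. The article gives 10 points as the minimally important difference and 17 as the assumed effect. A reader might infer that the result will be biased, or biased against PRP; the documents support neither. The dropout patterns and the 0.7 correlation are assumptions, and the illustration ignores the optional injection at 6 months, which may change how 6- and 12-month scores relate.

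**What to change.** Delete the completed-cases rule and state the analysis set as all randomised participants, analysed as allocated. Use every available 3-, 6- and 12-month iHOT-12 score, in a mixed model for repeated measures with baseline, arm, visit and arm-by-visit, or in an equivalent multiple imputation. Take the 12-month contrast as the primary result. State that treatment withdrawers who are still followed contribute their scores.

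Keep the completer t test as a sensitivity analysis, with completers defined as participants who have a 12-month score. Add a delta-adjusted check for data missing not at random, because the earlier scores remove bias only to the extent that loss depends on observed scores.

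The cost is a wording change and slightly more analysis in the software already named, with no new data, visits or participants. The downside is that the primary model then rests on a missing-at-random assumption, which the delta-adjusted check is there to probe.

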## Discussion

Platelet-rich plasma (PRP) is an autologous blood product, which has a higher concentration of growth factors postulated to provide enhanced healing and anti-inflammatory properties. There have been numerous studies on the efficacy of PRP in musculoskeletal soft tissue conditions with similar pathology to GTPS, with varying results, the most promising being in plantar fasciopathy and patellar tendinopathy. Corticosteroids are the established second-line treatment, but do not always work long term. PRP may be a suitable alternative to corticosteroid in GTPS, with longer-term effects; however, there are very few reports discussing its efficacy. Lee et al. in 2016 [26] prospectively studied the efficacy of intra-tendinous PRP injections as treatment for chronic recalcitrant gluteus medius tendinopathy. They found ultrasound-guided intra-tendinous PRP injections to be a safe and effective treatment option for chronic recalcitrant gluteus medius tendinopathy due to moderate to severe tendinosis. A second report by Ribeiro et al. from Brazil [23] was published in 2016 comparing the efficacy of PRP against corticosteroids. They concluded that during the first 2 months, which was the study period, the PRP has no influence on pain relief and functional improvement in trochanteric syndrome. Again in 2016 a third report from the USA compared ultrasound-guided percutaneous tendon fenestration to PRP injection for treatment of GTPS [27]. The report concluded that both ultrasound-guided tendon fenestration and PRP injection are effective for treatment of gluteal tendinosis, showing symptom improvement in both treatment groups. Large effect sizes were evident in these studies. We calculated these based on Cohen’s test, taking some statistical assumptions into account, given that all data were not available. The effect sizes in the study of Lee et al. were 1.303, 1.052, 0.883 and 1.677 for the mHHS, Hip Outcome Score (HOS) activities of daily living, HOS sport and HOT-33, respectively. The effect sizes in the study of Ribeiro et al. were 1.155, 1.371 and 1.509 for the Facial Expressions Scale for Pain at follow up of 10, 30 and 60 days.

Prior to these reports, Mautner et al. conducted a study in 2013 [28] to assess whether ultrasound-guided PRP injections are an effective treatment for chronic tendinopathies. The study included 180 patients of whom16 had gluteus medius tendinopathy. The majority experienced significant improvement in symptoms, evidenced by 82% of patients reporting at least moderate improvement of their symptoms. A similar satisfaction rate of 85%was also found, respectively, demonstrating that the improvement in symptoms likely resulted in patient satisfaction. There are no randomised trials in the current literature and all these published reports were based on short follow up periods and small numbers of patients.

This paper describes the rationale and design for the first randomised trial that aims to determine the effectiveness of PRP in the treatment of greater trochanteric pain syndrome. No previous trials have assessed PRP against placebo or measured clinical outcomes beyond 6 months. The HIPPO trial will make a significant contribution to the evidence base available to support effective conservative management of GTPS.

### Current status of the trial

The trial is currently running. Recruitment and treatment started in spring 2018.

## Abbreviations

bFGF: Basic fibroblast growth factor
BMI: Body mass index
CONSORT: Consolidated Standards of Reporting Trials
EQ-5D 3 L: Three-level version of the EuroQol five-dimensional questionnaire
GP: General practitioner
GTPS: Greater trochanteric pain syndrome
IGF: Insulin-like growth factor
iHOT-12: International Hip Outcome Tool-12
mHHS: Modified Harris Hip Score
NHS: National Health Service
NSAID: Non-steroidal anti-inflammatory drug
PD-EGF: Platelet-derived endothelial growth factor
PDGF: Platelet-derived growth factor
PI: Principal Investigator
PROM: Patient-reported outcome measures
PRP: Platelet-rich plasma
RCT: Randomised control trial
TGF: Transforming growth factor
VAS: Visual analogue score for pain
VEGF: Vascular endothelial growth factor
